### Two-year intervention

A second intervention is being carried out on a subset of children with isolated cleft lip with cleft palate, with an initially projected total of about 264 cases to be available for this subproject. Screening for eligibility and enrollment into the two-year subproject occurs at birth. Eligible children with clefts are randomized at birth into intervened or non-intervened groups. The pediatricians conduct a thorough clinical assessment of the development of intervened children every three months up to two years of age, including evaluation of physical growth (height, weight, and head circumference), neurodevelopment, using the Bayley Infant Neurodevelopmental Screener (BINS), and language, using the Receptive-Expressive Emergent Language Test (REEL). The BINS is used to monitor the course of an infant's development and identifies infants with developmental delays or neurological impairments who are in need of further diagnostic evaluation [21,22]. The REEL screens for delays in emergent speech and language development in medically and environmentally at-risk children [23,24]. The pediatricians also perform a dental assessment for the child and record erupted teeth and any abnormalities, check the nutritional status including feeding content, process, and problems, and inquire about all child morbidities and treatments since the last evaluation and overall changes in health and socioeconomics of family members (e.g. parental illnesses, changes in employment and marital status of the parents, and changes in schooling and health status of siblings). The pediatricians refer the intervened children to specialized health facilities and professionals based on their clinical assessments and the practice standards available for dealing with clefts and emphasize to parents the importance of compliance with these referrals. The pediatricians also provide counseling to parents in order to maintain a healthy and loving familial environment that provides continuous care to the child.

The healthy control children enrolled in the two-year study as a normal control group are matched to the non-intervened cleft group two to one at birth for sex, hospital, and week of birth. The non-intervened control group of children with clefts and the healthy control group receive the standard of care available in their respective community according to parental wishes. Both control groups are assessed at one and two-year follow-ups to measure study outcomes. The normal control group will be compared to the non-intervened cases with clefts to assess the impact of clefting on child health and family socioeconomic outcomes. The intervened and non-intervened cases with clefts will be compared to evaluate the effectiveness of the intervention in lowering the burden of clefting on the child and the family (see Figure 1).

#### Randomization procedures in the two-year study

The randomization of cases in the two-year study into intervened and non-intervened groups is based on a randomization sequence generated by the Data Center at the Research Triangle Institute (RTI) International, and is stratified by participating hospitals. The Data Center provides each pediatrician a set of sealed envelopes that contain a sheet indicating treatment assignment. The pediatrician administers the randomization procedure by assigning the next available envelope as each case is enrolled into the study. Study personnel and subjects are not blinded to the randomization assignments, but safeguards are in place to ensure that assignments are not known a priori. The pediatrician reports within 24 hours of each randomization to the Data Center the subject ID, the tracking number of the randomization envelope used, and the group assignment for verification, and any inconsistencies are readily corrected. The randomization sequence lists are kept in secure locations at the Data Center and ECLAMC headquarters.

### Study outcomes

The neonatal outcomes include overall mortality at 28 days of life (primary outcome), mortality in subgroups of isolated and non-isolated cleft groups, hospitalization days, and refinement of syndromic classification in the retrospective group. The impact of the neonatal intervention on infant mortality will also be evaluated and phone interviews are conducted with parents of prospective and retrospective groups when needed to inquire about child's survival at one year of age. The primary outcomes of the two-year study include overall neurodevelopment (measured by BINS) and weight changes. Secondary outcomes include performance on four ability areas including neurological functions/intactness, receptive functions, expressive functions, and cognitive processes (measured by the BINS), speech (measured by REEL), height changes, hearing, timing of cleft surgery, mortality, refinement in syndromic status classification, and emotional, social, and economic performance of the family.

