**Figure 1 F1:**
[figure not shown]
**Study Design**. Figure 1 presents a flowchart of the study design of the neonatal and the two-year subprojects. All infants born with a typical form of cleft lip and palate in the study hospitals are enrolled in the neonatal subproject. Only isolated cases with both cleft of lip and cleft palate who are singleton births, normal birth weight, and without complications other than cleft lip and palate that require systematic care are enrolled at birth in the two-year subproject and randomized into intervened and non-intervened groups. A group of healthy controls is matched to the non-intervened group by gender, date and hospital of birth at a ratio of 2 to 1. A = Evaluating the impact of the intervention on neonatal mortality. B1 = Evaluating the impacts of cleft lip and palate on child's development and family socioeconomic outcomes (Two-year subproject). B2 = Evaluating the impact of the two-year intervention on child development and family socioeconomic outcomes.

The two-year study group includes children from the neonatal prospective subgroup who are born with isolated forms of both cleft lip and cleft palate. Children with syndromic forms are excluded, as are twins and children with birth weight less than 2500 grams or who have complications other than cleft lip and palate that require systematic care. A group of healthy controls born without birth defects and subject to the same exclusion criteria and whose gestational age is between 37 and 42 weeks are also included in the two-year study.

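### The one-year mortality comparison is read as the effect of the neonatal intervention, but about a fifth of the prospective group also receives the two-year intervention during that year

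*Protocol article*

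**What the plan says.** All references are to the protocol article.

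- **Target (Study outcomes).** After the 28-day outcomes, the article adds a one-year one: "The impact of the neonatal intervention on infant mortality will also be evaluated". The data source follows: "phone interviews are conducted with parents of prospective and retrospective groups when needed to inquire about child's survival at one year of age". The groups are therefore the prospective and retrospective cohorts, and the difference is attributed to the neonatal intervention.
- **Overlap (paragraph after Figure 1).** "The two-year study group includes children from the neonatal prospective subgroup who are born with isolated forms of both cleft lip and cleft palate". Twins, infants under 2500 g, syndromic cases and infants with other conditions needing systematic care are left out of the two-year study, but they stay in the prospective group.
- **Timing (Two-year intervention).** "Eligible children with clefts are randomized at birth into intervened or non-intervened groups".
- **Content (Two-year intervention).** "The pediatricians conduct a thorough clinical assessment of the development of intervened children every three months up to two years of age". This is more than measurement: "The pediatricians refer the intervened children to specialized health facilities and professionals based on their clinical assessments". Nutrition checks and parental counselling are also part of it.
- **Comparator (Inclusion/exclusion criteria; Neonatal intervention).** The retrospective infants had routine community care and the ORIENT discharge guidance. They had neither study intervention.
- **Adjustment (Statistical analysis).** The example covariates are cleft type, baseline health and socioeconomic status, with allowance for hospital and country. Two-year assignment is not among them.

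**The concern.** Followed as written, the one-year comparison sets neonatal care, plus a second active intervention in some infants, against neither. Any effect of the second intervention on survival between the neonatal period and the first birthday would be credited to the first.

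The article does not treat that effect as nil. Mortality is listed among the secondary outcomes of the two-year study, and the Background links feeding problems and malnourishment in cleft infants to mortality risk. Adjusting for baseline confounders would not remove the effect, because the second intervention is a treatment given after birth to one cohort only. At stake is whether a one-year survival benefit, if seen, can be ascribed to four weekly visits in the first month.

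**Working it through.** **Plan's own figure.** None exists for this comparison: the article gives no one-year mortality rate, sample size or power. The steps below size the problem from the projected numbers and declared assumptions.

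**Inputs from the article.** Prospective group about 696 and retrospective group about 464 (Inclusion/exclusion criteria); two-year cleft cases about 264 (Two-year intervention); one-sided test at 0.05 (Power analysis).

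**Assumed inputs.** Allocation 1:1. Mortality *m* after the neonatal period that the two-year visits could still influence, 1% to 10%. Relative risk (RR) of death under the two-year care, 0.5 to 0.7.

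**Step 1: share affected.**
- In the two-year study: 264/696 = 37.9%.
- In its intervened arm: 132/696 = 19.0%.

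Only the second share matters. The non-intervened arm has community care after the first month, apart from outcome assessments at one and two years.

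**Step 2: shift in prospective one-year mortality if the neonatal intervention has no effect.** Shift = share × *m* × (1 − RR).
- Low: 0.190 × 0.01 × 0.3 = 0.0006, or 0.06 points.
- Middle: 0.190 × 0.05 × 0.5 = 0.0047, or 0.47 points.
- High: 0.190 × 0.10 × 0.5 = 0.0095, or 0.95 points.

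**Step 3: compared with sampling error.** At 25% mortality (a 28-day rate from Table 1, borrowed for illustration), SE = √[0.25 × 0.75 × (1/464 + 1/696)] = 0.026, or 2.6 points. The shifts are therefore about 0.02 to 0.37 of a standard error. With no neonatal effect, the probability of rejecting at one-sided 0.05 is:

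| Shift (points) | Rejection probability |
|---|---|
| 0.09 (*m* = 1%, RR = 0.5) | 0.054 |
| 0.47 | 0.072 |
| 0.95 | 0.10 |

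**Step 4: precision after the correction.** Removing the 132 intervened infants leaves 432 with weight 1 and 132 with weight 2. Effective n = (432 + 264)² / (432 + 132 × 4) = 484,416/960 = 505.

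Illustrative power at Table 1 rates (one-sided 0.05, pooled variance, no continuity correction):

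| Rates | All 696 | Intervened dropped, unweighted (564) | Weighted (about 505) |
|---|---|---|---|
| 0.20 vs 0.15 | 0.714 | 0.678 | 0.657 |
| 0.25 vs 0.20 | 0.642 | 0.607 | 0.587 |

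Table 1 itself gives 0.68 and 0.61 for these pairs. A continuity correction brings the calculation to 0.687 and 0.615, so the inputs agree with the article's.

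**The case against.** The strongest reply is that this is a condensed article. One-year mortality has one sentence, much of it about data collection. The logistic and Cox models are named for neonatal mortality, and the covariate list is introduced as examples. A fuller document could define the analysis set and handle the overlap. That stands as a caution about what the final analysis will do. It does not remove the mismatch in what is printed: the article names the effect to be estimated, and its own design prevents the named comparison from estimating it.

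Second, the effect is probably small. The affected infants are isolated-cleft singletons of at least 2500 g without other serious complications, and the Discussion expects isolated clefts to bear more on morbidity and development than on death. This stands, and makes the upper end of the range unlikely.

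Third, the two-year study compares mortality between its randomised arms, so the article provides separate evidence on the second intervention. This helps interpretation, but it does not correct the one-year estimate.

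Three stronger readings are tempting and are not supported:

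- **That the bias is worst in the isolated-cleft subgroup.** The isolated and non-isolated subgroups are specified for neonatal mortality. No one-year subgroup comparison is stated and no size for such a subgroup is given, so no figure can be attached.
- **That the primary outcome is compromised.** It is not, if the three-monthly visits start after day 28. The schedule suggests this, although the first visit date is not stated.
- **That correcting the overlap makes the one-year comparison unbiased.** It removes only the two-year component. The comparison with infants born in 2001 and 2002 remains historical and non-randomised.

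**Conclusion.** The point holds, as a modest one on a non-primary outcome. The one-year contrast between the prospective and retrospective groups does not isolate the neonatal intervention, because about 19% of the prospective group also receives the two-year intervention within that year and none of the retrospective group does.

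The likely distortion is 0.06 to 0.95 percentage points, favouring the neonatal intervention if the two-year care reduces deaths. The range rests on 1:1 allocation, post-neonatal mortality of 1-10% and a relative risk of 0.5-0.7, none of which the article gives. The attribution problem itself does not depend on the mortality or relative-risk assumptions; they only set its size.

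**What to change.** State how the one-year comparison treats infants randomised to the two-year intervention, by one of these routes:

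1. **Exclude and weight.** Leave out the intervened infants and weight the randomised non-intervened infants by the inverse of their allocation probability (2 if 1:1). Exclusion without weights would under-represent isolated cleft lip and palate. The cost is an effective prospective sample of about 505 in place of 696, which is roughly 0.06 of power in the illustration above.
2. **Model it.** Keep all infants in a Cox model with a term for two-year assignment acting after day 28, plus an indicator of two-year eligibility (isolated cleft lip and palate, singleton, at least 2500 g, no other condition needing systematic care) defined in both cohorts. Without that indicator the assignment term would absorb the lower risk of the infants selected for the two-year study. The cost is deriving eligibility for the retrospective infants from birth and medical records.
3. **Relabel, at minimum.** Report the all-infant one-year contrast as the effect of the combined programme. This costs a change of wording.

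Under any route, keep the 28-day primary comparison as it is, and say that the one-year result remains a historical comparison. No new data collection on the prospective group is needed.

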### Power analysis

The power analyses prepared prior to study initiation are reported in Tables 1 and 2 for the neonatal and the two-year subprojects respectively. The power estimation for the primary hypothesis of reduction in neonatal mortality in the prospective group compared to the retrospective control group assumes a simple random sample scheme and a probability of Type I error of 0.05. Power is estimated for alternative neonatal mortality rates in both the prospective and retrospective control groups due to the lack of robust estimates at the time of study initiation of baseline mortality rates in the retrospective group and of potential achievable reductions in neonatal mortality due to the intervention. Mortality rates of 20, 25, and 30% are assumed for the retrospective group. The neonatal mortality rate in the prospective group is also assumed to not exceed 25% and to be not higher than that of the retrospective group (one-sided test). The power calculation for the neonatal subproject is based on a sample size of 464 cases in the retrospective group and 696 cases in the prospective group. This analysis shows that acceptable power (>0.7) is available for reductions of about 30% or more in assumed baseline neonatal mortality rates (See Table 1).

**Table 1 T1:** Power to Detect Differences in Neonatal Mortality Proportions

*Neonatal Mortality in Retrospective Group*	*Neonatal Mortality in Prospective Group*	*Power*
0.20	0.12	0.97
	0.15	0.68
	0.17	0.34
0.25	0.15	0.99
	0.17	0.94
	0.20	0.61
	0.22	0.30
0.30	0.15	>0.99
	0.17	>0.99
	0.2	>0.99
	0.22	0.98

**Table 2 T2:** Power to Detect Differences in Means of Continuous Outcomes in the Two-Year Study

Sample Size per Group	Standardized Effect Size			
	0.15	0.25	0.4	0.5
60	0.30	0.60	0.92	0.98
90	0.40	0.76	0.98	>0.99
120	0.49	0.85	>0.99	>0.99
150	0.55	0.91	>0.99	>0.99
160	0.59	0.93	>0.99	>0.99
170	0.61	0.94	>0.99	>0.99

The power analysis to detect differences in means of the continuous outcomes of the two-year study (e.g. BINS and REEL scores or weight gain) between the study groups is also based on alternative effect sizes due to limited information available a priori on these parameters and on alternative sample sizes. In this analysis, power estimation assumes a paired sample where one subject is selected at random and another is a matched control (correlation of 0.5 between the subjects in a matched pair). Power is evaluated for standardized effect sizes (i.e. mean difference divided by standard deviation) of 0.15, 0.25, 0.4, and 0.5, using a Type I error probability of 0.05 and a one sided test. The analysis shows that acceptable power (>0.7) is available to detect a standardized effect size of 0.25 or higher with a sample size of 90 cases per study group. As an example, a 0.25 standardized effect size for the receptive language quotient of the REEL measure is equivalent to a 4-point difference from a mean score of 108 with a standard deviation of 16, which are reference estimates for samples of normal babies under 36 months of age.

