#### Inclusion/exclusion criteria

The neonatal prospective group that receives the pediatric intervention includes infants born with typical clefts of any etiology or affected segment (lip, gum, hard palate, soft palate) in participating hospitals between January, 2003 and December, 2005, and diagnosed as eligible within the first 48 hours after birth, with an initially projected total of about 696 cases to be available for recruitment. No other inclusion or exclusion criteria are imposed on this group. Since it was considered unethical to randomize neonatal subjects into treatment and no treatment control groups, as there was a strong sentiment that the intervention forms the current standard of care in the United States, a retrospective control group born in 2001 and 2002 with clefts in the same hospitals was chosen. This control group is projected to include about 464 cases, yet data are still being processed. This group of infants had previously received routine pediatric and medical care offered by their communities during the neonatal period. A schema of the study design is shown in Figure 1.

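### Table 1 overstates power at 30% baseline mortality: 0.98 for 0.30 v 0.22 should be about 0.91, and >0.99 for 0.30 v 0.20 should be 0.98

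*Protocol article*

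**What the plan says.** All the inputs to Table 1 ("Power to Detect Differences in Neonatal Mortality Proportions") are in the Power analysis section of the protocol article.

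- Sample size: "The power calculation for the neonatal subproject is based on a sample size of 464 cases in the retrospective group and 696 cases"; the second figure is the prospective arm.
- Sampling and error rate: the calculation "assumes a simple random sample scheme and a probability of Type I error of 0.05".
- Direction: prospective mortality is taken "to be not higher than that of the retrospective group (one-sided test").
- Control rates: "Mortality rates of 20, 25, and 30% are assumed for the retrospective group".

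At a retrospective rate of 0.30, the table gives power >0.99 for prospective rates of 0.15, 0.17 and 0.20, and 0.98 for 0.22. The section concludes from the table that "acceptable power (>0.7) is available for reductions of about 30% or more in assumed baseline neonatal mortality rates".

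**The concern.** Within the 0.30 block, power falls only from >0.99 to 0.98 as the prospective rate rises from 0.20 to 0.22. In the 0.25 block, the same drop of 8 percentage points (0.25 v 0.17) carries a power of 0.94. For a fixed difference, power should be slightly lower at the higher baseline, because the binomial variance is larger there. A figure of 0.98 for 0.30 v 0.22 therefore contradicts the table's own 0.94.

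Table 1 is the article's only power statement for the primary neonatal hypothesis. The text says that no robust baseline estimate existed, so a reader has to pick the row that looks most plausible and rely on it. A wrong row misstates the Type II error for that scenario. The article also says that it aims to help others plan similar studies, so the figure may be reused.

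**Working it through.** **Inputs** (Power analysis section): n1 = 464 retrospective, n2 = 696 prospective, one-sided alpha 0.05 (z = 1.645), independent binomial samples.

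**Formula.** With d = p1 − p2, k = 1/n1 + 1/n2 = 0.003592 and pooled rate p = (n1·p1 + n2·p2)/(n1 + n2):

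- SE0 = √[p(1 − p)k]
- SE1 = √[p1(1 − p1)/n1 + p2(1 − p2)/n2]
- continuity correction c = k/2 = 0.0018
- power = Φ[(d − c − 1.645·SE0)/SE1]; set c = 0 for the uncorrected version

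**Step 1: reproduce the table.**

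| Retrospective | Prospective | Printed | Corrected | Uncorrected |
|---|---|---|---|---|
| 0.20 | 0.12 | 0.97 | 0.973 | 0.977 |
| 0.20 | 0.15 | 0.68 | 0.687 | 0.714 |
| 0.20 | 0.17 | 0.34 | 0.337 | 0.366 |
| 0.25 | 0.15 | 0.99 | 0.993 | 0.994 |
| 0.25 | 0.17 | 0.94 | 0.942 | 0.950 |
| 0.25 | 0.20 | 0.61 | 0.615 | 0.642 |
| 0.25 | 0.22 | 0.30 | 0.300 | 0.324 |
| 0.30 | 0.15 | >0.99 | >0.999 | >0.999 |
| 0.30 | 0.17 | >0.99 | >0.999 | >0.999 |
| 0.30 | 0.20 | >0.99 | 0.984 | 0.987 |
| 0.30 | 0.22 | **0.98** | **0.910** | **0.920** |

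The corrected column follows the first nine rows to within about 0.01. The uncorrected column runs 2 to 3 points high in the mid-range rows. The continuity-corrected one-sided calculation is therefore very likely the one used.

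**Step 2: 0.30 v 0.22.** p = (464 × 0.30 + 696 × 0.22)/1160 = 0.252. SE0 = 0.02602, so 1.645·SE0 = 0.0428. SE1 = 0.02644.

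- Corrected: (0.08 − 0.0018 − 0.0428)/0.02644 = 1.339, power 0.910.
- Uncorrected: (0.08 − 0.0428)/0.02644 = 1.407, power 0.920.

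The Type II error is 0.08 to 0.09, against 0.02 as printed.

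**Step 3: 0.30 v 0.20.** p = 0.24, SE0 = 0.02560, 1.645·SE0 = 0.0421, SE1 = 0.02612.

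- Corrected: (0.10 − 0.0018 − 0.0421)/0.02612 = 2.148, power 0.984.
- Uncorrected: 2.216, power 0.987.

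**Step 4: could another method give 0.98 for 0.30 v 0.22?** One-sided at 464 and 696, an unpooled variance gives 0.916, the arcsine transform 0.920 and Fisher's exact test 0.910. Two-sided versions give 0.85 to 0.86. Swapping the arm sizes gives 0.920. Raising both arms to 696 gives only 0.961 uncorrected. None reaches 0.98.

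**Step 5: does the summary sentence survive?** For a reduction of exactly 30%, corrected, at 464 and 696: 0.20 v 0.14 gives 0.83, 0.25 v 0.175 gives 0.91, and 0.30 v 0.21 gives 0.96. All exceed 0.7.

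**The case against.** The strongest reply is that the error changes no conclusion. A fall from 30% to 22% is a 27% reduction (0.08/0.30) and still has power of about 0.91. The lowest-power block, at the 20% baseline, is printed correctly. The summary sentence stands, and neither the sample size nor the test depends on the wrong cell. All of this is right and limits the consequence, but the printed figure remains wrong by 6 to 7 points.

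It can also be said that >0.99 against 0.984 to 0.987 is close to rounding. That is fair: this cell is only a companion correction.

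Two stronger readings are tempting, and the documents do not support either.

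- *The entries slipped down one row.* The printed 0.98 is the right value for 0.30 v 0.20, so a reader might infer this. It rests on one coincidence, and nothing in the article shows how the entry arose.
- *The whole table treats a recruitable pool as the analysed sample, so the claim of power above 0.7 needs high participation.* The inclusion criteria describe the prospective number as "with an initially projected total of about 696 cases to be available for recruitment", which invites the inference. But only the 696 is described that way; the 464 is given as the projected size of the control group. No refusal or loss rate is stated, and an allowance for one is detail that an article may leave to the full protocol. As an assumed range, losing 0 to 40% of the prospective arm alone takes 0.20 v 0.14 from 0.83 to 0.74 (corrected), still above 0.7. Only equal losses of about 30% in both arms bring it to 0.69, and nothing in the article points to losses of that size.

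**Conclusion.** The power of 0.98 for 0.30 v 0.22 does not follow from the article's own inputs. It should be about 0.91 by the method that reproduces the first nine rows, or 0.92 without continuity correction. The neighbouring >0.99 for 0.30 v 0.20 should be 0.98, a minor discrepancy. This rests only on the stated sizes, the one-sided 0.05 level and independent binomial sampling; the choice among standard tests does not alter it. It is a local arithmetic error in the planning table for the primary neonatal hypothesis. It does not show that the study is underpowered, and the statement about reductions of about 30% or more remains true at 464 and 696.

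**What to change.** In Table 1, change the power for 0.30 v 0.22 from 0.98 to 0.91, and for 0.30 v 0.20 from >0.99 to 0.98. Leave the summary sentence as it stands. The cost is a correction of two cells; the stated power becomes slightly less favourable in one scenario, and no design, sample size or analysis changes.

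### The two-year power table assumes matched pairs with correlation 0.5, but the cleft arms are randomised and unpaired: at 90 per group and 0.25 SD, power is about 0.51, not 0.76

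*Protocol article*

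**What the plan says.** The Power analysis section introduces Table 2 as "The power analysis to detect differences in means of the continuous outcomes of the two-year study", naming BINS and REEL scores and weight gain as examples, between the study groups. It does not limit the table to one of the two planned comparisons. The assumptions are:

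- Design: "power estimation assumes a paired sample where one subject is selected at random and another is a matched control (correlation of 0.5" within each pair).
- Effect: "standardized effect sizes (i.e. mean difference divided by standard deviation) of 0.15, 0.25, 0.4, and 0.5".
- Test: "using a Type I error probability of 0.05 and a one sided test".

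The conclusion drawn reads: "acceptable power (>0.7) is available to detect a standardized effect size of 0.25 or higher with a sample size of 90 cases per study group". The Table 2 cell behind it is 0.76.

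The design is described elsewhere in the article:

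- Two-year intervention: "Eligible children with clefts are randomized at birth into intervened or non-intervened groups". About 264 such cases are projected.
- Randomization procedures in the two-year study: the sequence "is stratified by participating hospitals". No pairing is mentioned.
- Two-year intervention: the healthy controls are "matched to the non-intervened cleft group two to one at birth for sex, hospital, and week of birth".
- Statistical analysis: the two cleft groups are compared by simple tests and by regression that allows for hospital clustering. A paired analysis is not planned.

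**The concern.** The article makes two two-year comparisons. The effect of the intervention is tested by intervened against non-intervened cleft children. The burden of clefting is assessed by non-intervened cleft children against healthy controls. Only the second involves matching, and that matching is two controls to one case, not one to one.

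A pair correlation of 0.5 halves the variance of the mean difference compared with independent groups of the same size, so it acts like doubling the sample. The randomised comparison, which carries the two-year primary outcomes (overall BINS and weight change), cannot claim this gain, because no pairs are formed. If its power is overstated, a null result on BINS or weight may be read as showing that systematic care does not help, when the study had only about an even chance of detecting a 0.25 SD effect at the sample size the article cites.

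**Working it through.** **Inputs from the article.** One-sided alpha 0.05; standardised effect d = 0.25; n = 90 per group; assumed pair correlation 0.5; stated power 0.76 (all from Power analysis and Table 2). About 264 cleft cases are projected (Two-year intervention). The allocation ratio is not stated, so 264/2 = 132 per arm assumes an equal split.

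**Step 1: reproduce the stated figure.** For pairs with correlation ρ, the SD of the difference is SD × √(2(1 − ρ)), which equals SD when ρ = 0.5. The noncentrality is d√n = 0.25 × √90 = 2.372.
- Normal approximation: Φ(2.372 − 1.645) = 0.766.
- Noncentral t, 89 df: 0.761, matching the stated 0.76.

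The same formula reproduces the other cells of Table 2 within about 2 points. The one slightly larger gap is n = 150, d = 0.15 (stated 0.55, computed 0.57). The method behind the table is therefore not in doubt.

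**Step 2: two independent groups.** The noncentrality is d√(n/2) = 0.25 × √45 = 1.677.
- Normal approximation: Φ(1.677 − 1.645) = 0.513.
- Noncentral t, 178 df: 0.510.

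Across the n = 90 row (one-sided 0.05):

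| Effect (SD) | Table 2 (paired) | Independent groups |
|---|---|---|
| 0.15 | 0.40 | 0.26 |
| 0.25 | 0.76 | 0.51 |
| 0.40 | 0.98 | 0.85 |
| 0.50 | >0.99 | 0.96 |

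Down the d = 0.25 column:

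| n per group | Table 2 (paired) | Independent groups |
|---|---|---|
| 60 | 0.60 | 0.39 |
| 90 | 0.76 | 0.51 |
| 120 | 0.85 | 0.61 |
| 150 | 0.91 | 0.70 |
| 160 | 0.93 | 0.72 |
| 170 | 0.94 | 0.74 |

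**Step 3: the projected sample.** At 132 per arm and d = 0.25, independent groups give 0.65; the paired formula would give 0.89. At d = 0.25, power of 0.70 needs 152 per arm and 0.76 needs 178 (noncentral t; the normal approximation gives 151 and 177).

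**Step 4: detectable effect.** With independent groups, 0.70 power corresponds to about 0.325 SD at 90 per arm and 0.27 SD at 132 per arm. At 90 per arm, 0.76 power corresponds to 0.35 SD. On the article's REEL example (SD 16), 0.325 SD is 0.325 × 16 = 5.2 points, against the 4 points quoted.

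**Step 5: could hospital stratification supply the correlation?** The article gives no within-hospital correlation. With 264 cases over 47 hospitals there are about 264/47 = 5.6 cases per hospital. If sharing a hospital acted like a pair correlation of 0.05 to 0.20 (an illustrative assumption), power at d = 0.25 would be 0.53 to 0.59 at 90 per arm and 0.67 to 0.73 at 132. Reaching 0.70 at 90 per arm needs a correlation of about 0.41. Recovering Table 2 needs 0.5.

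**Step 6: the healthy-control comparison.** With two controls per case, the variance per matched set, in units of SD², is 1 + (1 + ρ)/2 − 2ρ. For 90 sets and d = 0.25 (normal approximation):
- ρ = 0.05: variance 1.425, power 0.63.
- ρ = 0.20: variance 1.20, power 0.70.
- ρ = 0.50: variance 0.75, power 0.86.

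**The case against.** The strongest points on the other side are these.

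- **Table 2 contains no miscalculation.** It follows from an openly stated assumption. This stands: the fault is that the assumption does not fit the design.
- **The pairing language suits the healthy-control comparison.** At the article's own correlation of 0.5, ignoring the second control makes Table 2 conservative there (0.76 against 0.86). This also stands. For that comparison the complaint reduces to a 1:1 table being used for a 2:1 design, with no support given for 0.5. The lower figures in Step 6 rest on a correlation range that the article does not supply. But the text does not confine Table 2 to this comparison, and if that was the intent, the randomised comparison has no stated power at all.
- **132 per arm is not a fixed ceiling.** It is a projection under an assumed equal split. Correct, and it is labelled so here.
- **The planned regressions could recover power.** Covariates or strata explaining about 13% of outcome variance (1 − 132/152) would bring 132 per arm to 0.70 at 0.25 SD, so the study is not shown to be underpowered at its projected size. At the cited 90 per arm, about 41% (1 − 90/152) would be needed, and Table 2 invokes no such adjustment.
- **Estimates and Type I error are unaffected, and larger effects remain detectable.** True: at 0.40 SD, 90 per arm still gives 0.85. The article's claim, however, is made at 0.25 SD.

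None of this rescues the stated claim for the randomised comparison.

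**Conclusion.** The concern holds. For intervened against non-intervened cleft children, power above 0.7 at 0.25 SD with 90 per group rests on pairs that the design does not form. Unadjusted power is about 0.51 against the stated 0.76, a shortfall of 25 percentage points. At the projected 264 cases, split equally, it is about 0.65, still below the article's own threshold of 0.7.

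These figures assume a one-sided 0.05 test (as in the article), equal arms, no loss to follow-up, and no gain from covariates or stratification. Modest gains could lift the projected sample to about 0.70, but they would not plausibly rescue the claim at 90 per arm. For the healthy-control comparison, Table 2 is the wrong layout but not necessarily optimistic; that depends on a correlation for which the article gives no basis.

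**What to change.** Replace Table 2 with two tables:

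1. Intervened against non-intervened cleft children: two independent groups, stratified by hospital, including the projected number per arm and stating the allocation ratio. Any gain claimed from stratification or covariates should be shown as an explicit, sourced assumption.
2. Non-intervened cleft children against healthy controls: 1:2 matched sets, over a range of correlations with a reason given for the range. Values from 0 to 0.2 alongside 0.5 would show how far the answer depends on this choice.

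Then restate the conclusion in Power analysis: without adjustment, 90 per arm gives about 0.51 power for 0.25 SD in the randomised comparison, and power above 0.7 needs about 0.33 SD at 90 per arm or 0.27 SD at 132. The REEL illustration should be changed to match.

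The cost is one recalculation and some rewording. No extra patients and no change to the design or analysis are needed, but the stated power becomes less favourable.
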